#### Dropout criteria

Patients who refuse to participate in the study visits for personal reasons or those whom the researchers are unable to contact through all available means will be regarded as dropouts.

#### Termination criteria

Patients will be removed from the study if they develop severe liver or kidney damage during the trial (ALT or AST exceeding twice the normal upper limit, acute kidney injury), severe clinical discomfort caused by the drug (such as severe nausea and vomiting, severe dizziness, and headache), and severe drug allergies. All criteria and decisions will be jointly determined by two or more physicians with the title of deputy chief or higher.

Potential trial participants will be recruited from the six hospitals listed in Supplement Table 2. To reach the target sample size, the trial will be advertised in living communities by local healthcare professionals. We will also utilize advertising via brochures, flyers, or other means suggested through the clinic sites as appropriate. Before each interview, we described the aims of the study, guaranteed confidentiality, and obtained written informed consent. The interviews and examinations were achieved on the premises of the treatment hospital.

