## Methods and design

### Study design

This study is designed as a double-blind, randomized, three-group-parallel, placebo-controlled superiority trial. One hundred and twenty patients with IgA nephropathy will be recruited, and the overall study design will be divided into two phases. In the pre-randomization phase, all participants will be confirmed to have received at least 3 months of RAAS blocker therapy to ensure that the patients have reached optimal blood pressure control (130/80 mmHg, the ideal range specified by the KDIGO2012 clinical practice guidelines) or have received the maximum tolerated dose of ACE inhibitor or ARB before entering the next phase. After qualification confirmation and informed consent, the enrolled patients will enter the post-randomization intervention phase. All participants will be randomly divided into the ART 100-mg group, ART 50-mg group, and placebo group for 6 months of intervention.

The flow diagram of the study process is shown in Fig. 1. Each participant will be assigned eight visits, including 3 months before the randomization (visit 1), 2 months before the randomization (visit 2), 1 month before the randomization (visit 3), randomization (visit 4), 1 month after the intervention (visit 5), 2 months after the intervention (visit 6), 3 months after the intervention (visit 7), and 6 months after the intervention (visit 8). The schedule for enrollment, intervention, and assessment is shown in Table 1. Retention of patients is promoted by close and frequent contact with their nutritional counselor and study physician via telephone, email, and study visits. In case of relevant issues, visits outside the study schedule are offered.

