#### Withdrawal criteria

The subjects who no longer meet the inclusion criteria, have poor compliance, need immunosuppressive therapy, or have any other reason for violation of the protocol will be monitored by the investigators. These patients will be required to continue regular study visits as scheduled in the protocol after discontinuation of treatment. The data that need to be recorded is the end-point events and safety data that occurred during the duration of this trial.

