### Safety assessment

The safety assessment includes any serious adverse event and any general adverse event according to the WHO acute and subacute side effects of the performance and indexing criteria for assessment [24]. All records, including adverse events and laboratory test results from the subjects, will be evaluated and followed up until resolved by a medically qualified investigator. The patient’s vital signs and any clinical discomfort will be monitored throughout the study period. Patients who are harmed during this study will receive the necessary medical treatments, such as changing the treatment plan, dealing with complications on time, etc., and the appropriate insurance will cover the expenses.

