### Sample size

This is a double-blind, randomized, three-group-parallel, placebo-controlled clinical study, and the sample size estimates were based on the change in proteinuria levels. According to the study results when using similar types of drugs (HCQ) for the treatment of IgA nephropathy [12, 25], the average baseline proteinuria was 2.0±0.8 g/day, and 36 participants in each arm could provide 90% of the detection ability, assuming that the placebo group level of proteinuria had not changed, and the ART treatment detected a 25% reduction in proteinuria (ART group: 0.5±0.5 g/day). Assuming that the two doses of the ART group has the same efficacy (the ratio of the ART group to the placebo group is 2:1), and a 10% dropout rate with a type I error rate of 0.05, we plan to enroll 120 participants (40 in each group) in the study.

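### Patients who meet the toxicity criteria are removed from the study rather than only from study drug, so their month-6 outcomes would go unmeasured and be filled by LOCF

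*Protocol article*

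**What the plan says.** The protocol article sorts patients who leave the planned course under three headings and treats them differently.

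- **Withdrawal criteria** cover loss of eligibility, poor compliance, need for immunosuppression and other protocol violations. For this group, "These patients will be required to continue regular study visits as scheduled in the protocol after discontinuation of treatment". On what is collected: "The data that need to be recorded is the end-point events and safety data" occurring during the trial.
- **Dropout criteria** cover "Patients who refuse to participate in the study visits for personal reasons" and patients who cannot be contacted.
- **Termination criteria** state that "Patients will be removed from the study if they develop severe liver or kidney damage during the trial", with ALT or AST above two times the upper limit and acute kidney injury as the markers. Severe drug-caused discomfort and severe drug allergy are also listed. Later visits are not mentioned.

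The primary outcome is the percentage change in proteinuria at 6 months (Outcome measurements). Visits after randomization fall at months 1, 2, 3 and 6 (Study design). The Statistical analysis section specifies ITT and fills missing values by LOCF.

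Two other statements bear on follow-up. Study design says: "In case of relevant issues, visits outside the study schedule are offered". Under Safety assessment, adverse events and laboratory results "will be evaluated and followed up until resolved by a medically qualified investigator".

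**The concern.** Of the three groups, the only one that the investigators themselves take out of the study is the one defined by harm. Stopping the drug is clearly right for these patients. Stopping measurement is a separate decision, and safety does not require it.

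If the wording is followed, the month-6 24-h proteinuria, UPCR and eGFR are not obtained. An ITT analysis would then rest on carried-forward values for patients whose outcomes the protocol chose not to collect. Several triggers are drug-related, so the loss may differ between arms. A patient removed for acute kidney injury could enter the month-6 eGFR comparison with a value from before the injury.

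An analysis plan can change how missing values are handled, but it cannot supply a measurement that was never taken. The point therefore has to be settled in the protocol.

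**Working it through.** **1. Which rule applies to whom**

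| Heading | Reason | Stated consequence |
|---|---|---|
| Withdrawal | Eligibility lost, compliance, immunosuppression, violation | Off treatment, scheduled visits continue |
| Dropout | Refusal or lost contact | Visits cannot be obtained |
| Termination | Liver enzymes, acute kidney injury, severe drug discomfort, severe allergy | Removed from the study; no visits stated |

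Terminated patients do not meet the dropout definition, and most of the triggers are not among the withdrawal reasons.

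**2. What would be carried forward**

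No visit is scheduled between months 3 and 6. The last scheduled proteinuria for a terminated patient is therefore from month 3 or earlier. If termination comes before month 1, it is the baseline value, which is a 0% change. Safety follow-up and unscheduled visits may yield later safety values, but neither provides for a month-6 24-h proteinuria.

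**3. The plan's own allowance**

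Sample size inflates 36 per arm for 10% dropout: 36/(1 − 0.10) = 40 per arm, and 3 × 40 = 120, as stated. That 10% refers to dropout, which the article defines differently. No termination rate is given.

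**4. Illustration of size**

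The termination rates and later changes here are assumptions.

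Let r be the share of an arm terminated, and d the change, in percentage points of baseline, between the last scheduled value and month 6. Then

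error in the arm's mean percentage change = r × d.

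| Terminated of 40 (r) | \|d\| = 0 | \|d\| = 12.5 | \|d\| = 25 |
|---|---|---|---|
| 2 (5%) | 0 | 0.625 | 1.25 |
| 4 (10%) | 0 | 1.25 | 2.5 |
| 6 (15%) | 0 | 1.875 | 3.75 |

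The largest d is set equal to the planned 25% reduction. The sign can go either way: LOCF may keep an early fall that is later lost, or miss a fall that comes later.

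**5. Effect on the ART–placebo difference**

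The sample size was set "assuming that the placebo group level of proteinuria had not changed". If that also holds for terminated placebo patients, d = 0 in that arm and the ART-arm error passes in full to the difference. As a share of the planned effect, the largest errors are 1.25/25 = 5%, 2.5/25 = 10% and 3.75/25 = 15%.

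**6. Scale against sampling error**

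The planned change of 0.5 ± 0.5 g/day from a baseline of 2.0 g/day converts roughly to an SD of 0.5/2.0 = 25 points. For 40 against 40, the standard error is 25 × √(2/40) = 5.59 points. The largest errors are then 1.25/5.59 = 0.22, 2.5/5.59 = 0.45 and 3.75/5.59 = 0.67 standard errors.

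**The case against.** The strongest objection is that everything turns on one verb. The article never says that month-6 tests are skipped. Removal from the study may be loose wording for stopping the drug, and this is a condensed article whose full protocol may say more. ITT analysis, the retention effort and the offer of extra visits all lean towards follow-up. This lowers confidence but does not dispose of the point. The Withdrawal criteria show that the authors knew how to write continued visits and did not do so here, and six hospitals could apply the wording differently.

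Second, the groups overlap. Acute kidney injury that takes eGFR below 30 also ends eligibility, and a terminated patient who later needs immunosuppression falls under Withdrawal as well. That is true, but the article does not say which rule prevails. Raised liver enzymes, drug discomfort and allergy remain outside the Withdrawal reasons.

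Third, the magnitude rests on assumed inputs. Acute kidney injury could move proteinuria by more than 25 points, so the upper figures hold only under that limit. Dividing 0.5 by 2.0 is also only a rough SD for individual percentage change when baseline itself varies (SD 0.8). Both criticisms stand. The figures show scale and are not estimates.

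Fourth, using values measured after rescue treatment is an estimand choice that an analysis plan may settle. That is fair, but the choice exists only if the values are collected.

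**Conclusion.** The point holds and should be fixed; confidence is medium because it depends on reading removal from the study in its ordinary sense. On that reading, the protocol gives up primary-outcome data for patients who leave because of harm, at a visit already planned, and LOCF fills the gap from month 3 or earlier.

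Neither the size nor the direction of the error can be obtained from the document. With 5% to 15% of an arm terminated, later change limited to 25 points and no change in terminated placebo patients, the error in the treatment difference is between 0 and 3.75 points either way. That is at most 15% of the planned effect. It is not shown that the trial's conclusion would change. The case for acting is that the loss is avoidable, plausibly informative and impossible to repair afterwards.

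**What to change.** In the Termination criteria, keep every trigger and the joint physician decision, but make the consequence permanent discontinuation of study drug with scheduled visits continuing as under Withdrawal criteria. State that 24-h proteinuria, UPCR and eGFR are measured through month 6 unless the patient withdraws consent. Say this explicitly, because the Withdrawal wording on what to record can be read as events alone. Use the observed values in the ITT analysis and impute only those that are truly missing.

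The visits and tests are already scheduled, so the cost is an amendment, ethics approval before it takes effect, and some effort to follow patients off drug. The estimated effect may be slightly smaller. On the stated dates (recruitment planned from 1 July 2021 to 31 December 2022, article published in May 2022), the change would fall during recruitment. Month-6 values already missed cannot be recovered, so it is better made early.

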### Participant recruitment

#### Inclusion criteria

The inclusion criteria for this study are (1) ages 18–75, (2) primary IgA nephropathy confirmed by renal biopsy, (3) persistent proteinuria ≥1.0 g/day after receiving adequate RAAS blocker treatment (proteinuria ≥1.0 g/day at visit 1 and visit 3), and (4) eGFR ≥30 ml/min per 1.73 m^2^ calculated by the Chronic Kidney Disease Epidemiology Collaboration (CKD-EPI) equation.

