### Statistical analysis

All results will be analyzed based on an intention-to-treat (ITT) analysis. Normally distributed data will be expressed as the mean ± standard deviation (SD), while nonnormally distributed data will be expressed as the median of the interquartile interval (IQR). Categorical data will be summarized as counts and percentages. The Shapiro-Wilk test will be performed to determine the normal distribution of continuous variables. For the comparison of baseline characteristics between groups, continuous variables (standard normal distribution) will be analyzed by a one-way ANOVA, continuous variables (nonstandard normal distribution) and ordered categorical variables will be tested by the Kruskal-Wallis *H* test, and unordered categorical variables or count variables will be tested by the chi-square test and Fisher’s exact test.

For the effectiveness outcomes, the primary outcome of proteinuria will be described by the percentage change of 24-h proteinuria test results at each visit from baseline, and the secondary outcomes of UPCR and eGFR will be described by the mean difference between the test results of each visit and the baseline. A paired-samples *t*-test or the Wilcoxon signed-rank test will be used for comparisons within groups at each visit time point from baseline, and one-factor ANOVA and the Kruskal-Wallis *H* test will be used for comparisons among groups at each visit time point.

For the safety indicators, adverse events will be described according to the number of cases and percentage, and the chi-square test and Fisher’s exact test will be used to analyze the differences between groups. The missing values will be filled up by the last-observation-carried-forward method. For the initial analysis, we will not adjust for confounders or stratification, and for the secondary analysis, we will adjust for confounders for subgroup analyses, such as baseline proteinuria (3 g/day), renal function (eGFR 45 m1/min per 1.73 m^2^), blood pressure level (systolic blood pressure 140 mmHg), MEST-C classification [26], and the new international risk-prediction score [27]. SAS 9.4 (SAS Institute Inc.) will be used as the statistical analysis tool. A 2-sided *P* < 0.05 will be defined as statistically significant.

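### Patients who meet a termination criterion leave the study and not only the drug, so obtainable month-6 values become LOCF imputations

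*Protocol article*

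**What the plan says.** The protocol article has three separate rules for patients who leave the planned course.

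- **Termination criteria:** "Patients will be removed from the study if they develop severe liver or kidney damage during the trial". The liver and kidney triggers are given as "ALT or AST exceeding twice the normal upper limit, acute kidney injury". Severe drug-caused discomfort and severe drug allergy are further triggers. Two or more senior physicians decide jointly.
- **Withdrawal criteria:** these cover patients who lose eligibility, comply poorly, need immunosuppression or otherwise violate the protocol. For them, "These patients will be required to continue regular study visits as scheduled in the protocol after discontinuation of treatment".
- **Dropout criteria:** these cover only refused visits and lost contact.

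The Statistical analysis section declares ITT for all results and adds: "The missing values will be filled up by the last-observation-carried-forward method". It makes no exception for terminated patients. The primary outcome is the percentage change in proteinuria after 6 months. Under Study design, the last two visits fall at month 3 (visit 7) and month 6 (visit 8), with none scheduled between them. The Safety assessment section says that adverse event and laboratory records "will be evaluated and followed up until resolved by a medically qualified investigator".

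**The concern.** Stopping the drug after a liver enzyme rise, acute kidney injury or severe intolerance is right. Ending the patient's participation is a different decision, and the Withdrawal criteria show that the authors know how to separate the two. For the termination triggers they do not.

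The patients affected have neither refused visits nor been lost, so their month-6 values could be obtained. The protocol itself makes them missing, for reasons linked to toxicity or kidney damage that may well differ between 100 mg, 50 mg and placebo. An ITT comparison is weakened when an imputed value replaces one that could have been observed.

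- **Proteinuria:** LOCF can carry an on-drug value past the point where the drug was stopped. This favours artesunate if the effect wears off.
- **eGFR:** an acute trough may be carried forward in a patient who recovers, or a pre-event value in a patient whose function later falls.

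The rules also collide. A patient whose acute kidney injury takes eGFR below 30 no longer meets inclusion criterion 4. The Withdrawal criteria then keep the visits and the Termination criteria end them. No priority is stated, so sites may treat the same case differently.

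**Working it through.** **The texts side by side.** Withdrawal means off treatment with visits continuing. Termination means removal from the study. With separate headings and contrasting wording, the second is hard to read as meaning off drug only. Nothing elsewhere in the article puts terminated patients back on the visit schedule. A patient removed after visit 7 and before visit 8 has no later scheduled measurement, so a month-3 value can enter the month-6 primary outcome.

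**The plan's own figures** (Sample size section): baseline proteinuria 2.0 ± 0.8 g/day, no change on placebo, a 25% reduction on artesunate (0.5 ± 0.5 g/day), 90% power, 36 per arm, 10% dropout, 40 per arm enrolled. Taking 0.8 and 0.5 as the two SDs, 1:1, two-sided 0.05:

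- n = (0.8² + 0.5²)(1.960 + 1.282)² / 0.5² = 37.4 per arm. Power at 36 per arm is 88.9%. Both are close to the stated 36 and 90%.
- 36 / 0.9 = 40 per arm, as stated.

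**Standard error of a 40 versus 40 difference:** √(0.8²/40 + 0.5²/40) = 0.149 g/day. Divided by the 2.0 g/day baseline this is 7.46 percentage points. The conversion is approximate because it treats baseline as fixed at its mean.

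**Proteinuria bias.** The protocol gives no removal rate, so these inputs are assumptions: k of 40 patients in one artesunate arm are removed, each having reached a share f of the planned 25% reduction, and each returns to baseline by month 6. LOCF credits them with 25f points that they no longer have:

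bias = 25 × f × k/40

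| f | k = 1 | k = 2 | k = 6 |
|---|---|---|---|
| 0 | 0 | 0 | 0 |
| 0.5 | 0.31 | 0.63 | 1.88 |
| 1 | 0.63 | 1.25 | 3.75 |

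In standard errors, the f = 1 row runs from 0.625/7.46 = 0.08 to 3.75/7.46 = 0.50. With f = 1 the mean change under full follow-up would lie between −24.4% (k = 1) and −21.25% (k = 6), while LOCF would report −25%. Removals on placebo do not offset this under the plan's assumption of no change on placebo.

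**eGFR bias.** If 1 to 2 of 40 patients carry an error of 10 to 20 ml/min per 1.73 m² (assumed), the arm mean shifts by 1 × 10/40 = 0.25 to 2 × 20/40 = 1.0, in either direction.

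**Observed month-6 values.** If the 10% allowance (4 of 40) is used up by dropouts as the Dropout criteria define them, 1 to 6 removals leave 40 − 4 − 1 = 35 to 40 − 4 − 6 = 30 observed values in that arm, against the planned 36.

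**The case against.** **Non-collection is inferred.** The article never says outright that visits stop. But that is the plain meaning of removal from the study when the preceding rule keeps other off-treatment patients on visits. The overlap example is narrow: acute kidney injury that leaves eGFR at 30 or above does not bring in the Withdrawal criteria on that ground.

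**Some measurements may still be made.** Events are followed to resolution, and Study design offers extra visits when issues arise. After acute kidney injury this would plausibly yield creatinine values, so safety information is not cut off entirely. Neither provision supplies a visit 8 24-h proteinuria or UPCR.

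**The effect is assumed and small.** This is fair. The 3.75-point figure needs 15% of an arm removed, every one of them at full response and every one returning fully to baseline. With 1 to 2 removals it is at most 1.25 points, under 0.2 standard errors. The requirement for a joint decision by senior physicians may also limit removals.

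**The direction is not established.** This also stands: the protocol gives no information on how fast an effect would wear off. Measured against the full planned effect, LOCF can look like attenuation. If 5% to 20% of artesunate patients were removed with none to half of the 0.5 g/day effect reached, the difference would be about 0.49 down to 0.40 g/day. That does not conflict with the table, which compares LOCF with what complete follow-up would have shown.

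**The 10% allowance may cover all attrition.** The Sample size section does not tie it to the Dropout criteria. If it includes removals, up to 4 per arm fit within the planned 36.

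**LOCF and the visit gap affect any missing patient.** True. What is specific here is that the protocol creates the missing values.

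**Conclusion.** The concern holds. As written, the termination rule produces avoidable missing outcome data for reasons of toxicity or kidney damage. It sits badly with the declared ITT analysis and overlaps with the Withdrawal criteria without a stated priority. An analysis plan cannot recover values that were never collected.

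The likely size is modest: 0 to 3.75 percentage points on the primary outcome, or 0 to 0.5 standard errors, if 1 to 6 of 40 artesunate patients are removed and return to baseline off drug. For eGFR it is 0.25 to 1.0 ml/min per 1.73 m² in either direction. All removal rates and post-removal courses are assumptions. The change should be made because it is cheap; nothing here shows that the primary result would be overturned.

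**What to change.** Keep the triggers and the two-physician decision. Amend the Termination criteria so that these patients are discontinued from study treatment but stay in the study, and extend the visit rule in the Withdrawal criteria to them through visit 8, covering 24-h proteinuria, UPCR, eGFR and the safety laboratory tests. Only withdrawn consent or lost contact should end participation. Analyse the observed values in the randomised arm, and impute only where a value could not be obtained.

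Patient protection is unchanged, because the drug still stops. The cost is a short amendment, the ethics approval and any participant notification that the Protocol amendments section requires, a reminder to the six hospitals, and a few already-scheduled visits for patients off drug.
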